**Fig. 1 Fig1:**
[figure not shown]
Graphical flowchart of the study design for NS (experiment I and II). In experiment I, patients with Noonan syndrome first receive lamotrigine (LTG) or placebo (PLC) with a minimum pause of 7 days and maximum of 60 days. In experiment II, lovastatin (LOV) or PLC with a minimum pause of 7 days and maximum 60 days. Between experiments, there will be a pause of at least 14 days

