### Interventions

Participants are randomized into either one out of the three approaches (exp. I–III). Three randomizations take place—one for each experiment. Patients are randomly assigned to receive either first verum then placebo, or vice versa. The randomization lists were created using RANCODE professional 2015. Randomization is performed block-wise. The randomization list was provided to the pharmacy for blinding, labelling and distribution of trial medication. For the case of emergency unblinding, a second set of sealed envelopes includes the information on the type of medication for each randomization number and is stored at the trial site. The integrity of the envelopes is monitored until end of study.

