#### Experiment II—Lovastatin (LOV) in patients with NS

Participants receive 200 mg LOV or placebo daily for 4 days prior to TMS. On the day of TMS, the medication is given 3 h before starting TMS corresponding to the peak plasma concentration of LOV [12]. After at least 14 (up to 60) days, a cross-over takes place: participants receive placebo or 200 mg LOV daily for 4 days prior to TMS (Table 1, Additional file 1). On the day of TMS, the medication is given 3 h before starting TMS.

**Table 1 Tab1:** Schedule of procedures and visits patient group 1, NS

*Study overview medication*	**Base-line (or day 1)**	**Visit 1 (day 1)** **D1**	**Visit 2 (min. 7—60 D after V 1)** **D8–61**	**Visit 3 (min. 14–60 D after V2)** **D22–121**	**Visit 4 (3 D after V3)** **D25–124**	**Visit 5 (min. 14–60 D after V4)** **D39–184**	**Visit 6 (3 D after V5)** **D42–187**
		**Exp. I: Lamotrigine (LTG) vs. placebo, single dose (with cross-over)**		**Exp II: Lovastatin (LOV) vs. placebo 4 days (with cross-over)**			
Informed consent	**X**						
Eligibility criteria	**X**						
Demographics	**X**						
Medical/surgical history	**X**						
Vital signs	**X**	**X**	**X**	**X**		**X**	
Pregnancy test^a^	**X**			**X**			
Randomization		**X**		**X**			
Exp. I: LOV or PLC) Four days				**X**	**X**	**X** **(cross-over)**	**X**
Exp. II: LTG or PLC) Single dose		**X**	**X** **(cross-over)**				
TMS (electromyography (EMG) integrated)^b^		**X**	**X**		**X**		**X**
TAP		**X**	**X**		**X**		**X**
Concomitant medication	**X**	**X**	**X**	**X**	**X**	**X**	**X**
AE/SAE		**X**	**X**	**X**	**X**	**X**	**X**

^a^To be performed after having obtained informed consent; if baseline is less than 5 days prior to V1, a second pregnancy test is not necessary

^b^TMS to be performed 3 h after intake of LOV and 2 h after intake of LTG

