#### Experiment III—Lamotrigine (LTG) in patients with NF1

Participants receive 300 mg single dose LTG or placebo 2 h before TMS [11]. After at least 7 (up to 60) days, a cross-over takes place: participants receive placebo or 300 mg single dose LTG 2 h before TMS (Table 2, Additional file 1).

**Table 2 Tab2:** Schedule of procedures and visits patient group 2, NF1

*Study overview medication*	**Baseline visit (or day 1)**	**Visit 1 (day1)** **D1**	**Visit 2 (7–60 days after V 1)** **D8–61**
		Exp. III: Lamotrigin (LTG) or Placebo	
Informed consent	**X**		
Eligibility criteria	**X**		
Demographics	**X**		
Medical/surgical history	**X**		
Vital signs	**X**	**X**	
Pregnancy test^a^	**X**	**X**	
Randomization		**X**	
Exp. III: LTG or PLC) Single dose		**X**	**X** **(cross-over)**
TMS (EMG integrated)^a^		**X**	**X**
TAP		**X**	**X**
Concomitant medication	**X**	**X**	**X**
AE/SAE		**X**	**X**

^a^To be performed after having obtained informed consent; if baseline is less than 5 days prior to V1, a second pregnancy test is not necessary

^b^TMS to be performed 2 h after intake of LTG

Experiments I and II take place with a sufficient time gap on the same set of patients (Fig. 1). It is not possible to conceal treatment in a triple cross-over design in group 1, which is why two separate tests have been planned on group 1.

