### Endpoints and endpoint rationale

The *primary endpoint* for each experiment is the difference between the amplitude of the motor evoked potential (MEP) elicited with transcranial magnetic stimulation (TMS, measured at three time points after interventional TMS for each investigation) after placebo and after medication (LTG and LOV).

Changes in MEP are a well-established and safe method to probe changes in cortico-spinal excitability in humans [18]. MEPs are elicited by TMS using a figure-of-eight coil with an outer diameter of 100 mm centred tangentially on the scalp over the primary motor cortex (M1) of the nondominant hand with its handle pointing in a posterior direction and laterally at an angle of approximately 45° away from the midline. MEPs are recorded from the abductor pollicis brevis (APB) muscle at rest by surface electromyography (EMG) using silver/silver chloride electrodes with a surface area of 263 mm^2^ (AMBU, Ballerup, Denmark) mounted in belly-tendon recording technique. Data are band-pass filtered (20–2000 Hz) and amplified using an Ekida DC universal amplifier (EKIDA GmbH, Helmstadt, Germany), digitized at 5 kHz sampling rate using a MICRO1401*mkII* data acquisition unit (Cambridge Electronic Design Ltd, Cambridge, UK) and stored on a standard personal computer for online visual display and later offline analysis using Signal Software version 5 (CED Ltd, UK). MEP size is determined by measuring the two highest peaks of opposite polarity. Twenty trials will be recorded and then averaged for each point of investigation as described elsewhere [15, 16]. Resting motor threshold is recorded to probe changes in local cortical excitability [19].

The *secondary endpoints* for each experiment include the difference between the neuropsychological testing of attention by the TAP and differences in short interval cortical inhibition (SICI) after placebo and after medication (LTG and LOV) [6, 20]. Another endpoint is the comparison of LTG and LOV effects on synaptic plasticity and attentional performance in the NS group. The TAP is a well-established tool and used to measure the influence of LTG and LOV on attention [7, 20]. We previously demonstrated that LOV leads to an amelioration of attentional performance in humans with NF1 [6]. Consequently, we hypothesized that this would also lead to better attention in patients with NS and that LTG ameliorates attention in NF1 and NS.

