**Table Tabb:** 

Experiment	Test number	Local significance level
I and II	1	0.025
I and II	2	0.013
I and II	3	0.008
III	1	0.050
III	2	0.025
III	3	0.017

Secondary endpoints and safety: Analyses of baseline and safety data and secondary endpoints will be done using appropriate descriptive statistics and paired sample tests for difference between the two study groups. All tests will be two-sided with an exploratory significance level of 5%. No adjustment for multiple comparisons will be done.

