## Discussion

The SynCoRAS study is targeting impairments in synaptic plasticity and cognitive impairment, one of the main health problems of patients with RASopathies. This has been done by the authors successfully for Lovastatin in NF1 before [6]. The obtained results will be transferred to patients with Noonan syndrome which demonstrated a reduced plasticity before as well [7]. Lamotrigine is most likely a more effective and promising substance improving synaptic plasticity and, consecutively, cognitive function [5, 10]. It is expected that both substances are improving synaptic plasticity as well as alertness. Changes in alertness may be a precondition for improvement of cognition. The strength of this project may be the short-term translation of results of basic science to human application and the provision of insights in pathophysiological mechanism. Results will be brought to practice through the tight connection to the large clinical centre for patients with cognitive impairment. Results might be used for the treatment of patients on an individual level as well as for the initiation of large clinical trials.

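### In Noonan syndrome patients lamotrigine is always tested before lovastatin, so the secondary comparison of the two drugs' effects is aliased with experiment order

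*Protocol article*

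**What the plan says.** Under *Endpoints and endpoint rationale*, after the per-experiment secondary endpoints, the protocol article adds: "Another endpoint is the comparison of LTG and LOV effects on synaptic plasticity and attentional performance in the NS group". The contrast is not defined further.

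The schedule for NS patients is in Table 1. The block headed "Exp. I: Lamotrigine (LTG) vs. placebo, single dose (with cross-over" covers Visits 1 and 2. The block headed "Exp II: Lovastatin (LOV) vs. placebo 4 days (with cross-over" covers Visits 3 to 6. TMS and TAP are done at Visits 1, 2, 4 and 6. Two rows of Table 1 swap the experiment labels, but their visit marks still put LTG first. The legend to Fig. 1 adds "Between experiments, there will be a pause of at least 14 days", and the closing paragraph under Experiment III says "Experiments I and II take place with a sufficient time gap on the same set of patients (Fig. 1".

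On randomisation, *Interventions* describes one list per experiment: "Patients are randomly assigned to receive either first verum then placebo, or vice versa". Nothing randomises or counterbalances the order of the two experiments. The opening sentence of the same section, read literally, allocates participants at random to one of the three experiments. That does not fit Table 1, nor an Experiment III defined by diagnosis.

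For secondary endpoints, *Analyses and statistics* gives descriptive statistics and "paired sample tests for difference between the two study groups", two-sided at an exploratory 5% level without adjustment. The *Discussion* expects a direction: "Lamotrigine is most likely a more effective and promising substance improving synaptic plasticity".

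**The concern.** LTG is always measured at TMS/TAP exposures 1 and 2, and LOV always at exposures 3 and 4. The earliest LOV measurement is day 25, which is 24 days after Visit 1. A difference between the drugs could therefore reflect the drugs, the position in the sequence, or both. No NS patient receives LOV first, so no analysis of these data can separate them, whatever an analysis plan says.

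At stake is the trial's only within-patient comparison of the two drugs. The article expects LTG to do better and intends the results to inform larger trials, but attaches no caveat about order to this endpoint.

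**Working it through.** **1. The plan's own figures.** No figure is given for the LTG–LOV comparison. The stated powers belong to the primary paired t-tests. With non-centrality (difference / 0.5) × √n, n − 1 degrees of freedom, differences 0.52 / 0.63 / 0.73 and the stated local levels, Experiments I and II give:
- n = 14: 89.6 / 95.0 / 97.9% (stated 89 / 95 / 97%)
- n = 12: 82.6 / 89.4 / 94.1% (stated 82 / 89 / 94%)

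Experiment III also agrees within one percentage point. Fixed experiment order does not enter these tests, because each compares verum with placebo inside one experiment.

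**2. What each contrast estimates.** Let s1 to s4 be additive shifts at the four TMS/TAP sessions, and let L and V be the true LTG and LOV effects against placebo. Assume verum/placebo order is balanced within each experiment.
- Raw: E(LOV session − LTG session) = V − L + (s3 + s4)/2 − (s1 + s2)/2. With a constant gain g per repeat, mean exposure is (1 + 2)/2 = 1.5 for LTG and (3 + 4)/2 = 3.5 for LOV, so the shift is 2g.
- Placebo-corrected: E(LTG − placebo I) = L + ½[(s1 − s2) + (s2 − s1)] = L, and likewise V in Experiment II. Additive shifts cancel on average.
- Placebo-corrected, with the second experiment's drug effect reduced by a fraction k: the LOV-minus-LTG contrast estimates V(1 − k) − L, a bias of −kV. LOV is never given first, so k cannot be estimated.

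**3. Size for a raw contrast (assumed inputs).** The documents give no practice effect. Suppose 2g equals 0.2 / 0.4 / 0.6 SD of the paired difference and the drugs are truly equal. A nominal 5% two-sided paired t-test (non-centrality d√n) then rejects:
- n = 12: 9.7 / 24.5 / 47.5%
- n = 14: 10.7 / 28.4 / 54.7%

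**4. Simulation of both contrasts (assumed inputs).** 12 patients, 5,000 runs, both true effects 0.6, SD 0.5 for the verum–placebo difference, session shifts 0 / 0.20 / 0.30 / 0.35. Bias is LOV minus LTG; rejection is at nominal 5%.

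| Scenario | Raw: bias, rejection | Placebo-corrected: bias, rejection |
|---|---|---|
| Fixed order, additive shifts | +0.22, 28% | 0.00, 4% |
| Fixed order, plus 50% weaker effect in second experiment | −0.08, 8% | −0.30, 24% |
| Random experiment order, additive shifts | 0.00, 3% | +0.01, 5% |
| Random experiment order, plus 50% weaker effect | 0.00, 5% | 0.00, 3% |

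These agree with the algebra: (0.30 + 0.35)/2 − (0 + 0.20)/2 = 0.225, and −0.5 × 0.6 = −0.30. Random experiment order leaves essentially no bias in either contrast.

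**5. Price of correcting for placebo.** With independent session errors of variance σ², the raw contrast has variance 2σ² and the corrected one 4σ², so the SD rises by √2. If the verum–placebo difference has SD 0.5, the corrected contrast has SD 0.5 × √2 = 0.71. At n = 12 the 95% half-width is 2.201 × 0.71/√12 = 0.45.

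**The case against.** The strongest reply is that the endpoint concerns drug *effects*, and the per-experiment endpoints in the same section are differences between medication and placebo. The natural reading is a comparison of placebo-corrected effects, in which additive practice effects cancel. The general reference to paired tests does not say that LTG sessions will be set against LOV sessions. This stands: the rejection rates in step 3 describe a contrast that the article leaves open but does not state.

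Further points also stand. The endpoint is secondary and exploratory in a phase IIa trial. A ceiling after repeated testing is plausible for TAP, but nothing in the article suggests one for MEP amplitude recorded at rest. Loss of patients after Experiment I does not by itself distort a within-patient contrast, because both drugs are then measured in the same people. The remark that a triple cross-over cannot be concealed explains why there are two experiments; it is not offered as a reason for their order. Recruitment has closed, so the order cannot be changed in this trial.

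What does not stand is the suggestion that this is only a detail for the analysis plan. The fixed order is a design feature stated here, and no choice of contrast removes the aliasing. Nor does the sentence about allocation to one of three experiments help, since Table 1 gives all NS patients one sequence.

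**Conclusion.** The point holds in a limited form. In the NS group, drug is fully aliased with experiment position, so the LTG–LOV comparison has no randomised basis. Raw sessions would carry any session effect in full. Placebo-corrected effects remove additive effects on average, but stay biased if the drug effect changes with position, for example through a TAP ceiling or carry-over between experiments. The documents give nothing from which to size that bias; all figures in steps 3 and 4 rest on assumed inputs, and even the sign of a raw bias depends on them.

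A reader might infer that any LTG–LOV difference is simply test experience, or that the planned test has a false-positive rate of 10 to 48%. The documents do not support either: each experiment has its own placebo session in randomised order, and a raw session comparison is nowhere specified. Nor is there any consequence for the primary tests or the sample size.

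**What to change.** **For the data already collected** (wording only):
- Define the endpoint as the within-patient contrast (LTG − placebo of Experiment I) − (LOV − placebo of Experiment II), in NS patients with data from both experiments. Do not compare raw LTG and LOV sessions.
- State that the comparison is non-randomised and aliased with order, and draw no conclusion about which drug is superior.
- Report placebo II − placebo I only as a descriptive check for additive drift. It estimates (s3 + s4)/2 − (s1 + s2)/2, which already cancels in the corrected contrast, and does not test whether the drug effect changes with position.
- Reconcile the *Interventions* sentence about allocation to one of the three experiments with Table 1.

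**For the design, now in practice a successor trial:** randomise NS patients 1:1 to Experiment I first or Experiment II first, keeping both experiments, their blinding and the pause between them as they are. This costs one extra randomisation list, with no extra visits or patients.

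The downside is precision: the placebo-corrected contrast has about twice the variance of a raw one under the assumptions of step 5. The article reports 16 participants enrolled across both diseases without the split, so the NS number may be below the 12 used there.

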For SICI, a subthreshold conditioning stimulation is delivered 2, 3 and 5 ms before a test stimulus [6]. It has been demonstrated before that an increased inhibition is the most prominent factor in mice with NF1 to prevent synaptic plasticity [5]. The authors have previously demonstrated that LTG is a potent modulator of synaptic plasticity in healthy humans [10]. Decreasing intracortical inhibition by LOV was associated with an increase in synaptic plasticity in patients with NF1 [6]. The central role of intracortical inhibition regulating synaptic plasticity in NF1 has recently been certified by animal studies revealing a new option of pharmacological intervention with LTG [5]. We have previously shown that LOV leads to a disinhibition in patients with NF1 and, therefore, hypothesized that this would be a key factor to normalize cortico-spinal excitability in patients with NF1 and NS.

*Safety measures* include documentation of blood pressure and heart frequency prior to the intervention as well as monitoring of EMG activity during TMS intervention and documentation of adverse events (AE), severe adverse events (SAE) and suspected unexpected serious adverse reactions (SUSAR) following established definitions and legal requirements. The intensity of AEs is defined according to the common terminology criteria for adverse events (CTCAE Version 4.0, https://www.eortc.be/services/doc/ctc/CTCAE_4.03_2010-06-14_QuickReference_5x7.pdf).

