### Risk/benefit analysis

There are known side effects of lovastatin (LOV) and lamotrigine (LTG). LOV and LTG are used in an off-label context and in a higher dosage as recommended in the Summary of Product Characteristics (SMPC) of the medicinal products. However, all side effects of the medication (LOV and LTG) have been described after longer application whereas in the present study patients will receive LOV only four times and LTG only one time. In one patient receiving LTG, a mild rash following the administration reported has been reported [21]. In an own placebo-controlled, randomized, double-blind study using the same single dose of LTG (300 mg), no side effects, apart from mild sedation/dizziness and lacrimation have been reported in 26 young healthy adults [10]. LTG has been well tolerated in another TMS study using dosages up to 325 mg [11]. Severe skin reactions such as Stevens-Johnson syndrome, toxic epidermal necrolysis, drug rash with Eosinophilia and systemic symptoms (DRESS) syndrome or aseptic meningitis occurring 8 weeks after long-term application of LTG have never been mentioned after single-dose application. These adverse events can be excluded to the actual state of knowledge.

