A 4-day course of LOV has been used in an own study in *n* = 11 patients with NF1 and is not expected to provoke any side effects [6]. It has been shown that doses of 200 mg of LOV were proven to be save in adult human volunteers [22]. Moreover, accidental overdoses up to 6 g have been tolerated with no specific symptoms and recovery without sequelae. Adverse events of LOV occur after longer application (> 1–2 weeks). Overall, the treatment with LTG and LOV in the context of the present study is not expected to provoke any side effects. A randomized, placebo-controlled long-term study investigated the effect of simvastatin, another 3-hydroxy-3-methyl-glutaryl-coenzyme A (HMG-CoA) reductase inhibitor, on cognition in children with NF1 [23]. This study did not find effects of simvastatin on cognition in children with NF1 [23]. In the present study, LOV will be used to investigate its effects on synaptic plasticity and attentional performance in patients with NS. We previously demonstrated in a randomized, placebo-controlled trial effects of LOV on synaptic plasticity and attentional performance in patients with NF1 in short-term use [6]. Moreover, another study demonstrated effects of lovastatin in children with NF1 undergoing a dose escalation protocol for 3 months on verbal and nonverbal memory [24]. This may highlight potential pharmacological differences of LOV and simvastatin.

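### The NF1 schedule has no vital-signs check at cross-over Visit 2, where placebo-first participants take their only 300 mg lamotrigine dose

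*Protocol article*

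**What the plan says.** The safety paragraph under Endpoints and endpoint rationale names the "documentation of blood pressure and heart frequency prior to the intervention", together with EMG monitoring during TMS and adverse-event documentation. It makes no exception for either disease group.

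Two visit tables turn this into a schedule:

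- Table 1, "Schedule of procedures and visits patient group 1, NS", marks vital signs at baseline and at Visits 1, 2, 3 and 5. Visits 1 and 2 are the two lamotrigine/placebo dosing days of Experiment I. Visits 3 and 5 open the two four-day lovastatin/placebo courses of Experiment II.
- Table 2, "Schedule of procedures and visits patient group 2, NF1", marks vital signs at baseline and Visit 1. Visit 2, 7 to 60 days later, has no mark in that row. It does have marks for the cross-over dose, TMS, the attention battery, concomitant medication and AE/SAE.

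The Interventions section randomises each participant to verum then placebo or the reverse. The Risk/benefit analysis says that both drugs are used off-label and "in a higher dosage as recommended in the Summary of Product Characteristics".

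**The concern.** Experiments I and III give the same drug at the same single dose, with the same cross-over and the same TMS two hours later. The safety check before dosing should therefore be the same. In Experiment I it is scheduled on both dosing days; in Experiment III on the first only, and no reason is given.

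The gap falls on an identifiable group. An NF1 participant randomised to placebo first has vital signs taken on the placebo day and none scheduled on the lamotrigine day. Because the order is blinded, site staff cannot pick these participants out for an extra reading. At stake is a routine pre-dose check before a dose that the article itself describes as above the recommended one.

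**Working it through.** No sample size, power or alpha figure is involved. The check is a cell-by-cell comparison and a short count.

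**1. Treatment period by treatment period**

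| Experiment | Period start | Treatment starting at that visit | Vital signs marked? |
|---|---|---|---|
| I (NS) | Visit 1 | Lamotrigine or placebo, single dose | Yes |
| I (NS) | Visit 2 | Cross-over dose | Yes |
| II (NS) | Visit 3 | Lovastatin or placebo, four days | Yes |
| II (NS) | Visit 5 | Cross-over course | Yes |
| III (NF1) | Visit 1 | Lamotrigine or placebo, single dose | Yes |
| III (NF1) | Visit 2 | Cross-over dose | **No** |

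Five of the six period starts carry the check. The exception is NF1 Visit 2.

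**2. Which event the reading precedes.** In Experiment II, TMS is done at Visits 4 and 6, and vital signs are not marked there. They are marked at Visits 3 and 5, when dosing begins. So the schedule ties the reading to the start of dosing, not to TMS. On that reading NF1 Visit 2, a dosing visit, should have one.

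**3. Is the blank cell an extraction fault?** Five other rows of Table 2 keep their Visit 2 marks (dose, TMS, attention battery, concomitant medication, AE/SAE). The column is intact, so a lost mark is unlikely.

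**4. Age of the last scheduled reading at NF1 Visit 2.** Visit 1 is day 1. Visit 2 is 7 to 60 days later: 1 + 7 = day 8 and 1 + 60 = day 61, which matches the table's own D8–61. The last scheduled reading is therefore 7 to 60 days old.

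**5. Number affected as planned.** Inputs: 14 NF1 participants (Analyses and statistics) and an assumed 1:1 order. 14 / 2 = 7 would take lamotrigine at Visit 2 with no scheduled same-day reading. In Experiment I the number is 0 of 14, because both dosing days are covered.

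**6. Number affected as enrolled.** Trial status gives 16 enrolled without the split by disease. If neither group exceeded its planned 14, NF1 enrolment lies between 16 − 14 = 2 and 14. Half of that is about 1 to 7, provided that all of them reached Visit 2.

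**The case against.** **The safety sentence may mean one reading before treatment starts.** It is in the singular and does not say before each dose; baseline and Visit 1 would then satisfy it. This is a fair reading of the sentence alone, and it softens the conflict between text and table. It does not explain why Table 1 repeats the check at each period start, including the equivalent lamotrigine cross-over visit. The difference between the two tables is the firmer ground.

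**It may be a table slip and not a gap in conduct.** This is plausible. Table 1 swaps the experiment labels in its two dosing rows. Table 2 attaches the pregnancy-test footnote to the TMS row and leaves its TMS footnote unused. The full protocol is not shown. The article therefore establishes what was scheduled in print, not what was done.

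**Other safeguards remain.** AE/SAE recording and concomitant medication are marked at NF1 Visit 2, and EMG is monitored during TMS. The article ties no threshold or dosing decision to the vital signs. This stands and keeps the point small.

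A reader might also infer three stronger points that the article does not support:

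- *That the paired safety analysis has no pairs for vital signs in Experiment III.* The plan provides that "Analyses of baseline and safety data and secondary endpoints will be done using appropriate descriptive statistics and paired sample tests", without naming vital signs. Step 2 above shows the reading to be pre-dose, so even two readings per participant would not compare on-drug with on-placebo values.
- *That the pregnancy test is inconsistently scheduled.* The Visit 2 cell is blank for this row too, but Table 1 likewise has no test at Visits 2 and 5, so the tables agree. The footnote that "if baseline is less than 5 days prior to V1, a second pregnancy test is not necessary" covers only the interval from baseline to Visit 1 and sets no limit for Visit 2. Inclusion criterion 5 requires approved contraception or no capacity to bear children. A repeat urine test is at most an optional safeguard.
- *That the check was dropped because "the treatment with LTG and LOV in the context of the present study is not expected to provoke any side effects".* The article does not give this as a reason. The same Risk/benefit section already discloses the mild effects seen with a single 300 mg lamotrigine dose. Rewording that sentence would be editorial.

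**Conclusion.** The point holds as a minor safety-schedule inconsistency. Table 2 omits the vital-signs check at NF1 Visit 2. This does not fit the listed safety measure or the schedule for the same drug and dose in Noonan syndrome.

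Its size is about 7 of 14 planned NF1 participants, assuming 1:1 order. Monitoring at that visit is reduced, not removed. The article gives no frequency of side effects for the dose, so no risk can be estimated. Nothing here bears on the MEP or attention results.

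The conclusion rests on reading the check as belonging to each treatment period, as Table 1 does, and on the printed table being the schedule in force. If the readings were in fact taken at Visit 2, what remains is an error in the table.

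**What to change.** Mark a pre-dose vital-signs check at Visit 2 in Table 2. At the design stage this costs one extra blood pressure and heart rate reading per NF1 participant.

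Trial status reports that the last visit has taken place, so for this trial:

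1. Check the Experiment III case report forms for Visit 2 readings.
2. If they were taken, correct Table 2.
3. If they were not, state the omission as a limitation when safety is reported. Readings not taken cannot be recovered.
4. Schedule the check at every dosing visit in the follow-on trials that the article foresees.

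The cost now is a search of existing records and either a one-cell correction or a one-sentence limitation.
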